### Study Protocol

#### Recruitment

Patients in the department of cardiac surgery who underwent cardiac surgery with cardiopulmonary bypass will be assessed for eligibility for the study according to the inclusion and exclusion criteria. Additionally, the control group will be recruited from people who will have health checks at Peking Union Medical College Hospital or the healthy volunteers. When people agree to participate, the informed consent forms will be signed in duplicate. Recruitment will be terminated when the case group reaches 60 cases. The study protocol was approved by the Ethics Committee. The committee will oversee the study to monitor data safety. The collection started on August 1, 2018 and is expected to finish on September 30, 2020. We have collected a total of 67 samples, including 45 cases of cardiac surgery patients in the case group and 22 healthy people in the control group have been collected on January 31, 2020.

#### Sample Collection

There will be 60 patients enrolled as the case group and 30 healthy people as the control. After fasting for at least 6 h but not more than 10 h, venous blood will be collected by direct venepuncture or established venous access from patients enrolled. Plasma will be taken from the blood and remain in Eppendorf tubes at −80°C for 1 h. Fresh fecal samples will be obtained (sometimes aided by glycerinum) and stored at −80°C before analysis. In the control group, samples will be collected once. In the case group, feces and blood samples will be acquired at the following time points (Figure 1): (1) T1: 1 day before cardiac operation; and (2) T2: within 24–72 h of ICU admission, sampling must be performed before patients start oral feeding.

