#### Definition

The clinical criteria according to the third international consensus (Sepsis-3) (17):

Sepsis: suspected or documented infection and an acute increase of ≥2 SOFA points.

Suspected infection group will be identified as those who had body fluids sampled for culture and received antibiotics but had a negative culture result.

The documented infection group will be identified as those who had body fluids sampled for culture with a positive result.

Survivors: Patients that survive for 28 days or more after surgery.

Non-survivors: Patients that survive <28 days after surgery.

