#### Metabolomics Analysis

The blood and stool samples will be analyzed using untargeted metabolomics. The analysis will be performed on an ultra-high-performance liquid chromatography system. To detect as many metabolites as possible, we plan to perform both polar ionic and lipid modes depending on the properties of the serum metabolites. The raw data will be converted into mzXML format and then processed by XCMS (20) software for peak picking and alignment. Metabolite features generated from XCMS will be further quantified by metaX software (21), including missing value imputation, data filtering, normalization, and comparison. Significant metabolites will be calculated using univariate (T/Wilcoxon test) and multivariate (PCA and PLS-DA) analyses integrated in metaX. The online HMDB database (22) and KEGG database (19) will be used to annotate the polar ionic metabolites by matching the exact molecular mass. The MS/MS spectrum from HMDB, MassBank (23) and an in-house database will assist in metabolite identification. For lipid identification, a LipidBlast database (24) will be used by matching the MS/MS spectrum and retention time. MetaboAnalyst (25) will be used for the identification of metabolic pathways.

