### Multi-Omic Data Analysis Plan

The data will be analyzed according to the case and control groups, sepsis and non-sepsis groups, and survivor and non-survivor groups, or some other classifications based on the pathophysiology.

Metagenomic and metabolomics statistical analysis will be performed using commercial software. To account for dependencies in repeatedly measured observations within a subject, a linear mixed-effect model will be used to assess the differences between the case group and the control group. Statistical analysis will be performed using SPSS (version 22, SPSS, Chicago, IL). A two-sided significance level of 0.05 will be used for statistical inferences. Combining principal component analysis (PCA), partial least squares discriminant analysis (PLS-DA), and orthogonal partial least square discriminant analysis (OPLS-DA), different metabolite profiles will be identified.

Receiver operating characteristic (ROC) analysis will be conducted to evaluate the utility of the potential biomarkers selected. Multivariate logistic regression analysis will be used to show the correlation between each factor and prognosis and changes in intestinal flora. A *p* < 0.05 will be considered statistically significant.

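### The stated metabolite selection does not separate administered substances from host or microbial metabolites, so a treatment-derived feature can be selected as a biomarker

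*Protocol article*

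**What the plan says.** **Assay.** Under Metabolomics Analysis: "The blood and stool samples will be analyzed using untargeted metabolomics". The stated aim is breadth: "To detect as many metabolites as possible, we plan to perform both polar ionic and lipid modes".

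**Selection.** The same section names t/Wilcoxon tests, PCA and PLS-DA as the way to find significant metabolites, with no covariate. Data filtering is named only in general terms. Multi-Omic Data Analysis Plan then adds: "Receiver operating characteristic (ROC) analysis will be conducted to evaluate the utility of the potential biomarkers selected". That section also plans a mixed model for repeated measures and a logistic regression. Neither names drug exposure.

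**Timing.** Under Sample Collection, patients are sampled one day before surgery (T1) and again in the ICU: "T2: within 24–72 h of ICU admission, sampling must be performed before patients start oral feeding". The fasting rule, "After fasting for at least 6 h but not more than 10 h", does not address intravenous drugs or parenteral nutrition. For blood: "venous blood will be collected by direct venepuncture or established venous access from patients enrolled". For stool: "Fresh fecal samples will be obtained (sometimes aided by glycerinum".

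**Exposure.** Under Definition, the suspected-infection part of the sepsis group had cultures taken and "received antibiotics but had a negative culture result". Under Study Population, anti-infective treatment before surgery is an exclusion, and so are certain unspecified medications in controls. Observation and Data Recording lists antibiotics, vasoactive drugs and enteral or parenteral nutrition, recorded at ICU admission and at each sampling.

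**The concern.** An untargeted assay does not by itself distinguish a compound that was given from one that the host or the flora made. If a substance is given more often in one of the compared groups, its features separate the groups without carrying any information about metabolism. The stated selection would pass such a feature on to ROC analysis on the same terms as any other.

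The Study Design section promises predictive biomarkers. A drug given because infection is suspected cannot predict sepsis before treatment starts. The comparison of patients with healthy people, which Grouping by Outcomes calls primary, is also exposed wherever it uses T2 samples.

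**Working it through.** **How exposure relates to each contrast**

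- *T1 versus T2.* Anti-infective treatment before surgery is excluded. T2 falls in the ICU, where the plan itself records antibiotics, vasoactive drugs and nutrition. Exposure differs by structure.
- *Patients versus controls.* Controls are healthy and are screened for certain medications. Exposure differs by structure for T2 samples.
- *Sepsis versus non-sepsis.* All of the suspected-infection subgroup received antibiotics by definition. The documented-infection definition does not mention antibiotics, and non-sepsis patients may also receive them. Exposure may differ, but the documents do not say by how much.

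**Size**

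The plan gives no figure on this point, so there is none to reproduce. Inputs from the plan: 30 sepsis, 30 non-sepsis, 30 controls (Study Design), and two-sided 0.05 (Multi-Omic Data Analysis Plan). The exposure shares p1 and p2 are assumptions.

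Model: the feature is absent in unexposed people, and has the same lognormal intensity in exposed people of either group. It has no link to biology. Then

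AUC = p1(1 − p2) + ½[p1·p2 + (1 − p1)(1 − p2)] = 0.5 + (p1 − p2)/2.

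For example, 0.5 + (0.90 − 0.40)/2 = 0.75.

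Share of repeats with p < 0.05, at 30 versus 30 (Wilcoxon on intensity by simulation, 4,000 runs; Fisher on presence or absence by exact enumeration):

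| p1 | p2 | AUC | Wilcoxon | Fisher |
|---|---|---|---|---|
| 90% | 40% | 0.75 | 94% | 98.5% |
| 70% | 40% | 0.65 | 57% | 56% |
| 90% | 70% | 0.60 | 27% | 37% |
| 90% | 80% | 0.55 | 10% | 10% |
| 50% | 50% | 0.50 | 5% | 3% |

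Wilcoxon is one of the planned tests; Fisher is shown only for comparison.

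For 60 cases at T2 versus 30 unexposed controls:

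| Cases exposed | AUC | Flagged (either test) |
|---|---|---|
| 10% | 0.55 | about 25% |
| 20% | 0.60 | about 93% |
| 30% | 0.65 | at least 99% |

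**One sensitivity.** These figures give all unexposed samples the same value. I repeated the simulation with small random background values in unexposed samples. The 90% versus 40% Wilcoxon result hardly moved (93%). The case–control result at 20% exposed fell to about 33%, and at 30% to about 67%. The case–control figures therefore depend on how absent values are filled in.

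**The case against.** The strongest reply is that this is a condensed article. Line-draw procedure and rules for dropping drug features are details that a laboratory manual or analysis plan would carry, and their absence alone is no finding. Data filtering is named, compounds are to be identified against several databases, and a parent drug would probably be recognised at that stage. The exposures are recorded, and a logistic regression is planned. The Discussion acknowledges that antibiotics, catecholamines, proton-pump inhibitors and feeding alter gut bacteria.

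Much of this stands. It removes any complaint about blood-draw handling. It does not remove the point about selection, because there the article is specific: it names the tests, the software and the ROC step, and no exposure term appears in any of them. Drug metabolites are also less surely recognised than parent drugs.

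Two stronger readings are tempting.

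- A reader might infer that T2 blood is drawn through running infusion lines. The text says only established venous access. It gives no share of samples, and does not say that an infusate runs through the access or that the route differs between sepsis and non-sepsis patients.
- A reader might infer that drugs track sepsis by definition. Antibiotics are required only for the suspected-infection subgroup. The SOFA rise can come from components other than vasoactive drugs. With high exposure in both groups the effect nearly vanishes, as the 90% versus 80% row shows.

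A multiplicity correction would also reduce the problem. At 0.05/1000, simulation flagged essentially none of the case–control features at 20% exposed, but 92% at 50%. The article states only 0.05.

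**Conclusion.** The point holds in limited form. Followed as written, the selection can report treatments as biomarkers. The risk is clearest for T1 versus T2 and for patients at T2 versus controls, where exposure differs by structure. For sepsis versus non-sepsis it is conditional on unequal exposure: from near-certain flagging at a 50-point gap to about 10% at a 10-point gap, and no more than the nominal 5% with no gap.

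All of these sizes rest on assumed exposure shares, on the assay detecting the substance at all (the documents do not say which drugs it picks up), and on the simple present-or-absent model. This does not show that the eventual findings will be drugs. It shows that the stated rule would not prevent it. The change is worth making because it is cheap and uses data already planned.

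**What to change.** 1. **Metabolomics Analysis:** before group tests, PLS-DA and ROC, annotate features with the HMDB and MS/MS resources already planned. Remove those that match the recorded antibiotics, vasoactive drugs or nutrition components, the glycerin used for stool, or their known metabolites. Alternatively, flag them and analyse them separately. Report how many were set apart.
2. **Multi-Omic Data Analysis Plan:** as a sensitivity analysis, repeat the selection adjusted for, or stratified by, recorded antibiotic, vasoactive-drug and parenteral-nutrition exposure.
3. Report exposure shares by group, so that readers can judge which row of the tables above applies.
4. Where the draw route happens to be on record, use it only in a sensitivity analysis. A uniform route is not needed for this point, and 45 of the 60 cases had already been collected by 31 January 2020.

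**Cost:** one filtering step and one repeated analysis, both possible on stored data. A few endogenous compounds that are also administered, such as catecholamines, amino acids and lipids, are lost or set apart; flagging rather than deleting limits that loss. With 30 per group, strata will be small, so the adjusted analysis should be read as a check and not as a replacement.

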## Abstract

**Introduction:** Fever of unknown origin (FUO) and hemodynamic instability are complications that develop after cardiac surgery combined with cardiopulmonary bypass (CPB) for heart disease. Patients who develop fever with hemodynamic instability after cardiac surgery may have systemic inflammatory response syndrome or sepsis. Cardiopulmonary bypass (CPB) is a technique that temporarily takes over the function of the heart and lungs during cardiac surgery. Recent reports suggest that early bloodstream infections of patients undergoing CPB are due to gram-negative bacteria that are present in the intestinal flora. The theory of intestinal flora translocation has growing evidence. Intestinal ischemia-reperfusion that occurs during cardiac surgery with CPB will induce a systemic inflammatory reaction and may cause intestinal flora translocation. Does this systemic reaction cause sepsis? We therefore propose this protocol to determine whether the changes in the intestinal flora in patients after cardiac surgery with CPB are related to sepsis.

**Methods and Analysis:** This study is a prospective observational case–control study to analyze the variation in the intestinal microflora and metabolites in patients undergoing cardiac surgery with CPB and to observe the outcomes of patients with routine clinical interventions. The control group will include healthy people without intestinal illness. Feces and blood samples will be acquired 1 day before cardiac surgery and within 24–72 h after cardiac surgery, and will be used for genomics and metabolomics analyses. Demographic data describing age, sex, main diagnosis, and past medical history and data related to the CPB time and application of antibiotics are available. Sequential (sepsis-related) organ failure assessment, infection-related laboratory items, infection site, and pathogenic microorganisms, and nutrition, and gastrointestinal function assessment are additionally recorded. Group analysis of data will be conducted according to the outcomes (sepsis vs. non-sepsis and survivors vs. non-survivors).

**Ethics and Dissemination:** This protocol has been ethically approved by the Ethics Committee of Peking Union Medical College (ID: ZS-1612). Informed consent will be obtained before subject enrolment, and data will be stored in a secured database. The results will be submitted to international peer-reviewed journals and presented at international conferences.

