### End Point

The observation and sample collection will be terminated after 28 days after surgery or for reasons of (1) death or if (2) the patient is satisfied with the indications for discharge from the ICU.

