#### Observation and Data Recording

Demographic data describing age, sex, main diagnosis, and past medical history are available at the inception of the study. Data related to the CPB time and application of antibiotics post-operation are available on the MUL-GM-CSCPB study Data Recording Sheet (Supplementary Table). The following observational data will be measured and recorded when patients are admitted to the ICU and at every sampling time.

Sequential (sepsis-related) organ failure assessment includes blood pressure; mean arterial pressure (MAP); and vasoactive drugs, including noradrenaline (NE), epinephrine (E), and dopamine (Dopa); PaO_2_/FIO_2_; Glasgow Coma Scale score; creatinine or urine output; bilirubin; and platelet count.Infection-related items include body temperature, WBC count, neutrophils, PCT, and antibiotics.Whether to be diagnosed with sepsis (according to Sepsis 3.0).Infection site and pathogenic microorganism.Nutrition and gastrointestinal function assessment including enteral or parenteral nutrition, bowel dilatation tested by ultrasound, gastric residual volume and intra-abdominal pressure measured via bladder.

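### T2 may be sampled anywhere from 24 to 72 h, and the stated t/Wilcoxon metabolite screen cannot separate sampling hour from sepsis; a low-severity point with a cheap remedy

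*Protocol article*

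**What the plan says.** All quotes are from the protocol article.

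- **Window and first stop** (Sample Collection): "2) T2: within 24–72 h of ICU admission, sampling must be performed before patients start oral feeding". The window is 48 h wide.
- **Second stop** (End Point): besides the 28-day limit, observation and sampling end "for reasons of (1) death or if (2) the patient is satisfied with the indications for discharge from the ICU".
- **Time origin** (Abstract): the same sample is described as "within 24–72 h after cardiac surgery", so the clock starts at surgery there and at ICU admission in Sample Collection.
- **Metabolite test** (Metabolomics Analysis): "Significant metabolites will be calculated using univariate (T/Wilcoxon test) and multivariate (PCA and PLS-DA) analyses integrated in metaX".
- **Contrasts** (Multi-Omic Data Analysis Plan): "The data will be analyzed according to the case and control groups, sepsis and non-sepsis groups, and survivor and non-survivor groups".
- **Other models** (same section): the linear mixed model is named for case versus control only. The remaining model is described as follows: "Multivariate logistic regression analysis will be used to show the correlation between each factor and prognosis and changes in intestinal flora". Its factors are not listed.
- **Recording** (Observation and Data Recording): "The following observational data will be measured and recorded when patients are admitted to the ICU and at every sampling time". The listed items include SOFA components, antibiotics and nutrition. The article does not list clock time among them.
- **Progress** (Recruitment): by January 31, 2020 the count stood at 67, "including 45 cases of cardiac surgery patients in the case group".

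**The concern.** A patient who recovers quickly reaches oral feeding or discharge readiness sooner and so has a shorter usable window for T2. Sepsis, as defined here, needs a rise of at least 2 SOFA points, so speed of recovery is plausibly related to group. Non-septic patients could then be sampled earlier on average.

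If a metabolite also changes between 24 and 72 h after admission, a two-group t or Wilcoxon test sees timing and sepsis as one difference. It may report a sepsis signal that is only timing, or miss a real one. The study intends to carry selected biomarkers into ROC analysis, so an unexamined timing difference would travel with them.

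**Working it through.** **Inputs from the article:** 30 sepsis and 30 non-sepsis patients (Study Design); two-sided 0.05 (Multi-Omic Data Analysis Plan); window 24–72 h (Sample Collection). The article gives no effect size, SD or power, so there is no figure of its own to reproduce.

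**Assumed, because the article gives neither:** the gap between groups in mean T2 hour (0, 6 or 12 h) and a linear metabolite drift (0.25 or 0.5 SD per 24 h).

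**Step 1. False-positive rate by formula, no true sepsis effect.**

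Spurious difference in SD units: δ = (gap / 24) × drift. Noncentrality: λ = δ × √(30/2) = 3.873 δ. The rejection rate is the probability that a noncentral t with 58 df exceeds 2.002 in absolute value.

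| Gap | Drift per 24 h | δ | λ | Error |
|---|---|---|---|---|
| 0 h | any | 0 | 0 | 5.0% |
| 6 h | 0.25 SD | 0.0625 | 0.242 | 5.7% |
| 6 h | 0.5 SD | 0.125 | 0.484 | 7.6% |
| 12 h | 0.25 SD | 0.125 | 0.484 | 7.6% |
| 12 h | 0.5 SD | 0.25 | 0.968 | 15.9% |

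With zero drift the error is 5.0% at any gap. The size does not depend on which group is sampled earlier.

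**Step 2. Simulation** (20,000 runs per setting, residual SD 1). Septic T2 hours are uniform on 24–72 h (mean 48 h). Non-septic hours are uniform on 24–60 h (mean 42 h, gap 6 h) or on 24–48 h (mean 36 h, gap 12 h). At a 12 h gap:

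| Drift per 24 h | t | Wilcoxon | Linear regression with hour |
|---|---|---|---|
| 0.25 SD | 7.7% | 7.1% | 4.7% |
| 0.5 SD | 15.2% | 14.1% | 5.0% |

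The simulation agrees with the formula, and the covariate restores the nominal level.

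**Step 3. A real difference hidden.** With a true 0.8 SD difference and drift against it, a 12 h gap cuts t-test power from 86% to 72% (0.25 SD) or 54% (0.5 SD). Adjusted power is about 75% in both cases.

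**Step 4. What adjustment costs.** With no drift, adjusted power at 0.8 SD is 84% at a 6 h gap and 75% at 12 h, against 86% for the t test. Suppose a hit were trusted only if significant in both analyses. When drift is absent or runs with the effect, about 5–10% of true hits would be flagged needlessly at a 6 h gap and 14–22% at 12 h.

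**Step 5. What that both-tests rule would buy.** At a 12 h gap it flags about 65% (0.25 SD) or 83% (0.5 SD) of false hits. However, it flags about 44% even with zero drift, simply because a second, noisier test must also be passed. Those percentages are therefore not all timing correction.

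**The case against.** The strongest objection is that no error has been shown. The article does not say that septic patients are sampled later, nor that any metabolite drifts over the window. Covariates and sensitivity analyses are commonly left to a full plan that is not shown here. Sampling before oral feeding is a sensible control for diet. The discharge stop matters only for patients ready before 72 h who have not yet been sampled. Other forces act against the presumed gap or in no stated direction: death can shorten sampling among the sickest, groups are formed after sample collection so sepsis arising after T2 would shrink a gap, and stool availability and the 6–10 h fast have no evident direction. The unlisted factors of the logistic regression could include hour.

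Most of this stands, and it lowers the severity. It does not remove the point, which concerns how stated choices combine: a wide window, two recovery-linked stops, and a named test with no term for hour. The logistic regression is described for prognosis and intestinal flora; nothing says that it replaces the metabolite screen.

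A reader might infer that the sepsis results will be biased, or that non-septic patients will be sampled earlier. The documents support neither. A reader might also take the 16% figure as an estimate. It requires all non-septic samples to fall in the first half of the window together with a 0.5 SD drift, and nothing in the documents suggests either.

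**Conclusion.** The point holds as a low-severity, inexpensive improvement. The planned t/Wilcoxon screen, applied to sepsis versus non-sepsis, cannot show whether sampling hour contributes to a difference, and no other stated analysis does so for metabolites. If a gap and a drift both exist, the per-metabolite error is about 6–8% at 6 h and 8–16% at 12 h, for drifts of 0.25–0.5 SD per 24 h. If either is absent it stays at 5%. These figures rest on assumed gaps, linear drift and 30 per group.

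The two time origins for T2 are a real inconsistency, but a matter of wording; they do not carry the point. There is no case for replacing the planned test, or for treating loss of significance after adjustment as proof of a timing artefact.

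**What to change.** 1. Use one time origin for T2 in the Abstract and in Sample Collection.
2. Compute hours from that origin to each T2 stool and blood sample, and report their distribution for sepsis and non-sepsis.
3. Keep the t/Wilcoxon screen as planned.
4. Prespecify a sensitivity analysis: a linear regression (or a rank-based one where Wilcoxon is used) of each T2 metabolite on sepsis, with T2 hour as a covariate.
5. Report the unadjusted and adjusted estimates side by side with confidence intervals. Judge timing by how far the estimate shifts, not by loss of significance alone. Also list metabolites that are significant only after adjustment, since timing can hide a difference as well as create one.

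**Cost:** a wording change, one table and one added regression, with no new patients or assays. The power of the planned test is unchanged. Narrowing the window is no longer a full remedy, because 45 of 60 case patients (75%) had already been collected by January 31, 2020.

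**Limits:** the adjusted estimate is less precise when the gap is large. If hour reflects severity, adjustment may remove real signal, which is why both results should be shown. The remedy depends on clock times being retrievable. ICU admission and sampling are already recording points, but the recording sheet is not shown.
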